**Fig. 2 Fig2:**
[figure not shown]
Consolidated Standards of Reporting Trials (CONSORT) flow diagram for Adolescent Coordinated Transition (ACT) trial site selection

### Study population

Study participants will be selected from among ALHIV enrolled in care at participating healthcare facilities.

#### Inclusion and exclusion criteria

Inclusion criteriaDocumented HIV infectionEnrolled in HIV care and taking ART at a designated ACT study siteAge 13–17 years: this allows for the following: alignment with target ages for routine transfer for healthcare facilities in Nigeria of 15- and 18-year-olds [14]; the pre-transfer 12-month transition period plus organized support group in the IG while CG is simply observed; and flexibility (albeit limited) in recruitment and study transfer age given the observed flexibility in age at transfer in actual practiceAware of HIV diagnosis

Exclusion criteriaUnable or unwilling to provide assent/consentNot medically stable

### Description of the ACT intervention

The ACT intervention is adapted and modified from the model described by Maturo et al. as shown in Fig. 3 [19]. The model is adapted to national guideline-recommended schedule of clinic visits every 3 months [31]. ACT has three main components:

**Fig. 3 Fig3:**
[figure not shown]
Adolescent Coordinated Transition (ACT) transitioning model showing the 12-month pre-transfer period (adapted from Maturo et al. [19])

Alternating pediatric-adult visits during the 12-month transition period that allows both adult and pediatric clinicians and the transitioning adolescent to address difficulties related to transition and adapt to the termination of the pediatric provider-patient relationship. Transition period clinic visits will be staggered as a Pediatric-Adult-Pediatric-Adult (PAPA) model with a target of four visits in totalA monthly peer-led organized support group (OSG) facilitated by trained young adults living with HIV and guided by a standardized six-module curriculum covering HIV Basics, Treatment and adherence, Support networks, Adolescent rights, Living positively, and Member choice. The OSG curriculum will address topics that will enhance the adolescent’s knowledge of HIV disease and how to self-manage their medical care. Overall, the OSG targets factors that may impact the patient’s transition readiness and psychosocial health measures. ALHIV will have the opportunity to contribute to curriculum content as their OSGs evolve and mature. The OSG will be initiated at enrollment and continued through the 12-month transition period, but to assess potential impact after transfer, it will be extended to the end of the follow-up period at 24 months post transferA case management team consisting of a physician, a nurse, and a trained patient advocate. Patient advocates already exist in these clinics and are usually HIV-infected adults who are selected based on exemplary treatment adherence and clinic attendance. The patient advocate will accompany study participants to all four PAPA clinic visits and will support the peer facilitator to lead the OSG

In the intervention arm, ALHIV will be transitioned from pediatric to adult care over a period of 1 year. Participants will be enrolled when they are approximately 1 year younger than the routine age of transfer at each study facility (either 15 or 18 years of age). During the 12-month pre-transfer period, ALHIV will be scheduled for clinic visits per the PAPA model. Patient advocates will accompany adolescents to each PAPA clinic visit. In addition, ALHIV receiving care at intervention sites will be encouraged to attend monthly OSG meetings. OSG meetings will be scheduled with routine clinic visits and at adolescent-friendly times to minimize logistical problems and to increase attendance and sustainability. Each OSG will include up to 25 participants.

### Description of the control condition/usual care

The usual “transition” of care for ALHIV in Nigeria is abrupt transfer to adult care. For this protocol, “transfer” is defined as immediate handover of the ALHIV from pediatric to adult care, without a transition period, and no formal or documented communication between pediatric and adult providers prior to, or after transfer. There is also no structured pre-transfer education and/or counseling provided to ALHIV and their caregivers with respect to procedures and expectations in adult care. In CG clinics, ALHIV will stop accessing pediatric care and start accessing the adult HIV clinic at the routine age of transfer at the facility. Adolescents will have access to all available services at the adult clinic including any adult support groups that may be available.

### Participant recruitment

The Standard Protocol Items: Recommendations for Interventional Trials (SPIRIT) Figure includes the timeline for study enrollment, intervention, and assessment (Fig. 4). Study participants will be recruited and enrolled onsite at the 12 study sites. Staff of the five participating local organizations will work with study site staff to identify eligible participants. The site staff will create a master list of eligible ALHIV aged between 13 and 17 years who are enrolled in HIV care at their specific site. Parents and guardians of eligible participants will be briefly informed about the study, and after indicating interest, will be approached by trained ACT research assistants for written informed consent at routine clinic visits during the recruitment period. Research assistants will thoroughly explain all study procedures and obtain consent. Assent will be obtained from eligible 13- to 17-year-old ALHIV wards of consenting parents/guardians. Written informed consent will be obtained from eligible ALHIV under 18 years old who are deemed mature or emancipated minors and meet the following criteria: have been granted the status of adulthood by a court order; have lived independent of parental guidance for a minimum of 1 year; are married; are living on the streets; or are the head of their household [32]. It is expected that recruitment will be completed between 1 July and 1 December 2017 (Additional file 1).

**Fig. 4 Fig4:**
[figure not shown]
Schedule of enrollment, interventions, and assessments

### Data collection

After obtaining informed consent and/or assent, research assistants will collect sociodemographic and medical history information onto enrollment forms by face-to-face interview with study participants and/or their caregivers. Four psychosocial health questionnaires (described below) will also be completed at enrollment by study participants. Completion of the four questionnaires will be repeated at 12, 18, 24, and 36 months after enrollment, coinciding with the transfer time point, and 6, 12, and 24 months post transfer, respectively (Table 1). Blood viral-load sampling will be performed on the same schedule, and the results of all viral-load tests will be reported to clinic providers and filed in participants’ medical charts for use in HIV management. Per national treatment guidelines, stable patients who have been on HIV treatment for at least 6 months should have at least one viral-load test every year [31]. Clinic visits will also be tracked to measure the primary outcome of retention in care.

**Table 1 Tab1:** Adolescent Coordinated Transition (ACT) study timeline, visits, and procedures

Visit	Timeline	Study visit	Procedure	Intervention group	Control group
Enrollment	0 months	Yes	Enrollment	Yes	Yes
			Readiness assessment	Yes	Yes
			Psychosocial assessment^a^	Yes	Yes
			Viral load	Yes	Yes
Visit 1	3 months	Yes	Type of clinic	Pediatric clinic	Pediatric clinic
			Organized support group	Yes	No
			Readiness assessment	Yes	Yes
Visit 2	6 months	Yes	Type of clinic	Adult clinic	Pediatric clinic
			Organized support group	Yes	No
			Readiness assessment	Yes	Yes
Visit 3	9 months	Yes	Type of clinic	Pediatric clinic	Pediatric clinic
			Organized support group	Yes	No
			Readiness assessment	Yes	Yes
Visit 4	12 months	Yes	Type of clinic	Adult clinic	Pediatric clinic
			Organized support group	Yes	No
			Readiness assessment	Yes	Yes
			Viral load	Yes	Yes
Transfer to adult care					
Visit 5	15 months	No	Type of clinic	Adult clinic	Adult clinic
			Organized support group	Yes	No
Visit 6	18 months	Yes	Type of clinic	Adult clinic	Adult clinic
			Organized support group	Yes	No
			Viral load	Yes	Yes
Visit 7	21 months	No	Type of clinic	Adult clinic	Adult clinic
			Organized support group	Yes	No
Visit 8	24 months	Yes	Readiness assessment	Yes	Yes
			Psychosocial Assessment^a^	Yes	Yes
			Viral load	Yes	Yes
End Visit	36 months	Yes	Type of clinic	Adult clinic	Adult clinic
			Readiness assessment	Yes	Yes
			Psychosocial Assessment^a^	Yes	Yes
			Viral load	Yes	Yes

^a^Psychosocial assessments performed with Health Locus of Control, Mental Health Continuum-Short Form, Functional Social Support Questionnaire and Sexual Risk Behavior, Beliefs, and Self-efficacy tools

In addition to collection towards evaluating the intervention’s effectiveness on primary and secondary outcomes, we will also collect data to describe and assess the implementation process, using the RE-AIM framework [28]. This will include: (1) Reach – the number and proportion of ALHIV willing to participate in ACT; (2) Adoption – the number and proportion of partner sites willing to implement the study; (3) Implementation – fidelity to the study protocol, including consistency of delivery of the alternating pediatric and adult clinic visits (PAPA); formation, curriculum adherence, and attendance at OSGs; presence and functionality of case management teams; and (4) Maintenance – the extent to which ACT becomes institutionalized at the intervention sites after completion of study follow-up [28].

### Outcome measures

The primary outcome measure is the *proportion of ALHIV retained in care at 12 and 24 months post transfer.* For this study, retention is defined as having made at least two clinic visits separated by a 6-month period within 12 months and at least four visits each separated by at least 6 months within 24 months post transfer. Hence, there are two primary outcome measures, with the long-term (24-month) retention measurement being a necessary “composite” of those who would have already demonstrated short-term (12-month) retention.

Secondary outcome measures are as follows:
*Proportion of ALHIV achieving viral suppression measured at 12 and 24 months post transfer*. Viral suppression is defined per the 2016 Nigerian national HIV guidelines as < 20 copies of HIV ribonucleic acid (RNA) per milliliter of blood plasma after at least 6 months of taking ART [33]
*Proportion of ALHIV demonstrating psychosocial wellbeing during study follow-up.* This study team has previously reported that poor psychosocial wellbeing and lack of adequate coping/self-efficacy skills are potential barriers to successful outcomes, including transitioning for this population in Nigeria [22, 34]. In order to generate more comprehensive evidence on wellbeing and resilience among ALHIV, we will administer four questionnaires among our study cohort: (1) the Health Locus of Control (HLC) scale will assess the extent to which ALHIV consider their health and health decisions to be within, or outside of their control; (2) the Mental Health Continuum-Short Form (MHC-SF) will measure the constructs of social, emotional, and psychological wellbeing; (3) the Functional Social Support Questionnaire (FSSQ) will evaluate the strength of the social support network of ALHIV; and (4) the psychosocial determinants of sexual risk behavior using the Sexual Risk Behavior, Beliefs, and Self-efficacy (SRBBS) scale will investigate for key psychosocial variables affecting ALHIV sexual risk-taking or protective behaviors [34–40]

The HLC tool has previously been validated by our research team among Nigerian ALHIV, and the MHC-SF has been validated among South African adolescents and adults [34, 40]. All the aforementioned tools will be administered by trained research assistants to study participants for a total of five times during the 3-year follow-up: at enrollment, transfer, and at 6, 12, and 24 months post transfer (Table 1). Additionally, healthcare transition readiness will be assessed twice (at enrollment and at transfer) using the Transition Readiness Assessment Questionnaire (TRAQ) [41, 42]. In a recent systematic review, the TRAQ was determined to be the best-validated transition tool with robust content and construct validity, as well as internal consistency [43].

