### Statistical analysis

For the primary objective, the study will assess the differential impact that the ACT intervention has on the primary outcome of retention. For this measure, ACT will test the difference in the percentage of study participants completing scheduled clinic visits under the hypothesis that the IG’s percentages will exceed CG percentages from baseline to 12 months (“short-term” retention) and to 24 months (“long-term” retention) following transfer to adult care. An initial test of proportions will be conducted at each time period to compare these percentages using a one-way test, and exact *p* values will be calculated using a permutation distribution. Additionally, a Poisson regression model with a time offset will be explored, which will allow for the development of a model to compare rates between the control and intervention arms while accounting for events (i.e., retention) per unit time, which allows time to vary for each subject as well as allowing the inclusion of potential covariates (for example, age, and time since HIV diagnosis).

Similarly, for secondary objective 1, the study will assess the differential impact that the intervention has on viral suppression. For this measure, ACT will test the difference in the percentage of study participants achieving viral suppression, under the hypothesis that the IG percentages will exceed CG percentages at each time period. The strategy in this analysis is similar to that of the primary objective: a one-way test of proportions will be conducted initially, followed by a Poisson count model to account for potential covariates of interest in addition to a temporal component.

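### The 24-month retention rule has almost no slack on 3-monthly visits, states no tolerance, and relies on visits that Table 1 does not list

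*Protocol article*

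**What the plan says.** Under Outcome measures, 12-month retention requires "at least two clinic visits separated by a 6-month period within 12 months" and 24-month retention requires "at least four visits each separated by at least 6 months within 24 months post transfer" (protocol article). Both are primary outcome measures, and the 24-month one is meant to be a subset of the 12-month one. No visit window, tolerance or day count for 6 months is given.

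On the visit schedule, the description of the ACT intervention states: "The model is adapted to national guideline-recommended schedule of clinic visits every 3 months". Table 1 lists post-transfer visits at study months 15, 18, 21, 24 and 36. Transfer follows the month-12 visit, so these are months 3, 6, 9, 12 and 24 post transfer. Nothing is listed between months 12 and 24 post transfer.

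On the data source, Data collection states: "Clinic visits will also be tracked to measure the primary outcome of retention in care".

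On the analysis, the Statistical analysis section says the trial will "test the difference in the percentage of study participants completing scheduled clinic visits", and calls the two time points short-term and long-term retention.

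In the intervention arm only, monthly support groups continue to 24 months post transfer, and "OSG meetings will be scheduled with routine clinic visits and at adolescent-friendly times".

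**The concern.** A retention measure should classify a person who never misses an appointment as retained. This one asks for a minimum spacing equal to exactly two appointment intervals, three times in a row, inside a fixed limit. If two visits that are nominally 6 months apart fall a day short, the next candidate is 3 months later, and the 24 months have room for only one such slip.

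At stake is misclassification on a primary outcome, in a trial of 216 participants in 12 sites. If engaged adolescents in both arms are scored as not retained because of calendar noise, the difference between arms will tend to shrink. The result would also depend on a day-count convention chosen at analysis. In addition, three parts of the article (the definition, Table 1 and the analysis text) do not describe the same measurement.

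**Working it through.** **Step 1: slack.** Inputs: four visits, gaps of at least 6 months, 24-month limit (Outcome measures); 3-monthly visits (Description of the ACT intervention). Minimum span = 3 gaps × 6 = 18 months. Available span = 24 − 3 = 21 months. Slack = 21 − 18 = 3 months, or one appointment interval.

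**Step 2: exact quarterly dates (3, 6, …, 24).** Five sets of four visits qualify: 3-9-15-21, 3-9-15-24, 3-9-18-24, 3-12-18-24 and 6-12-18-24. The rule is still met after any single missed visit (8 of 8 patterns) and in 18 of the 28 patterns with two missed. On whole-month dates the rule therefore works.

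**Step 3: Table 1 visits only (3, 6, 9, 12, 24).** Enumerating all subsets, the largest with gaps of at least 6 months has three visits, for example 6, 12 and 24. Four is reached (0, 6, 12, 24) only by counting Visit 4, which Table 1 places before transfer.

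**Step 4: full attendance with day-level scatter.** Assumptions, none given in the article: interval 91.3125 days (a quarter of 365.25), symmetric normal scatter, 24 months = 730.5 days. Scatter is either around fixed due dates or accumulates from one visit to the next. Qualifying visits are counted earliest-first, which gives the largest possible count. Share scored as retained at 24 months, 20,000 runs per row:

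| Scatter | SD (days) | Gap 182.6 d | Gap 180 d | Gap 168 d |
|---|---|---|---|---|
| Due dates | 3 | 16% | 51% | 100% |
| Due dates | 7 | 15% | 28% | 89% |
| Due dates | 14 | 16% | 22% | 58% |
| Accumulating | 3 | 24% | 65% | 100% |
| Accumulating | 7 | 23% | 41% | 96% |
| Accumulating | 14 | 23% | 31% | 72% |

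The 182.6-day column barely moves with SD. Two intervals make 2 × 91.3125 = 182.6 days, so each 6-month pair falls short about half the time however small the scatter. The month-24 visit likewise falls outside the limit about half the time.

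**Step 5: other assumptions.** With 84-day appointments and uniform scatter of ±7 or ±14 days, 0–8% pass at 180 or 182.6 days. If each visit is 0–14 days late and the next is booked from it, about 100% pass at 182.6 days. If the same lateness occurs around fixed due dates, about 4% pass.

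**Step 6: the 12-month rule.** Read as at least 182.6 days, 75–88% of the full attenders in Step 4 pass. The problem is mainly at 24 months.

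**Step 7: window alternative.** With at least one visit in each of the four 6-month windows, 100% pass in every row of Step 4, because a quarterly attender has about two visits per window. Table 1's rows alone would still leave the window from month 12 to month 18 empty.

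**The case against.** The strongest reply is that the article works in whole months, and in whole months its rule is met by every quarterly attender, even after one missed visit. The majority failure appears only with scatter and a strict day count that the article does not contain. Visit windows are a detail that a condensed article may leave to the full protocol or analysis plan. Retention is taken from tracked clinic visits, and Table 1 is not said to be the data source. The wording in Statistical analysis carries the retention labels and may be a loose paraphrase.

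Much of this stands. A reader might infer that the rule fails most adolescents who attend every visit, as a fact of the design. The documents do not support that: it depends on the assumptions in Step 4, and at 180 days with SD 3 or at 168 days most pass. A reader might also infer from Table 1 that the outcome is unattainable. It is not, because tracked routine visits in the second year can supply the fourth visit.

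A third tempting reading is that monthly support groups bias retention towards the intervention. That would require support-group days to be logged as clinic visits, and nothing in the text calls for it. The 12-month clause says clinic visits, and Table 1 keeps clinic type and support group on separate rows. It remains a conditional risk, because the 24-month clause says only visits and the groups are scheduled with clinic days.

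What does not fall away is that the article goes beyond omitting a window: it states a minimum gap of at least 6 months. Applied as printed to dated visits, that gap equals two appointment intervals with nothing to spare.

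**Conclusion.** Wrong as written, in a limited sense. From the document alone, the 24-month rule leaves 3 months of slack on a 3-monthly schedule and carries no tolerance. Table 1's post-transfer visits yield at most three of the four visits needed, and the analysis section names a different quantity. An adolescent can complete every scheduled visit and fail the definition, or miss one and pass.

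Under assumed scatter of SD 3–14 days, a literal reading scores 15–24% of full attenders as retained at 182.6 days, 22–65% at 180 days and 58–100% at 168 days. The width of that range is itself the problem: identical attendance is classified very differently according to a convention the definition leaves open. The effect on power or on the treatment difference has not been calculated, so no figure is claimed for it.

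**What to change.** Either of two definitions would do.

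- **Windows.** 24-month retention = at least one clinic visit in each of the four consecutive 6-month windows post transfer; 12-month retention = at least one in each of the first two. Nesting is automatic. The downside is that two visits can be nearly 12 months apart: visits at months 5.9, 6.1, 17.9 and 18.1 qualify despite a gap of 17.9 − 6.1 = 11.8 months. A sensitivity analysis with a maximum permitted gap should accompany it.
- **Spacing with a tolerance.** Keep the rule, state the day count for 6 months, and set a tolerance wide enough for quarterly visits. Step 4 shows that 168 days suffices for small scatter but not for SD 14. Nesting must then be made explicit. With a 168-day gap the second visit can fall as late as 730.5 − 2 × 168 = 394.5 days, after the 12-month limit.

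Under either definition, count clinic visits by the same rule in both arms and state that support-group attendance does not count. Reconcile Table 1 with the 3-monthly schedule so that it is clear which clinic visits between months 12 and 24 post transfer are abstracted. Use the same outcome wording in Statistical analysis.

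The cost is a change of wording, a registry update and abstraction of clinic visits already due to be tracked. The change should be fixed before any outcome data are compared by arm.

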### Sample size estimation

The design requires two arms (control = direct transfer without transition period or OSG and intervention = graduated transition with OSG). Six geopolitical zones are included in the design, with two sites (one replicate per arm) located in each zone. The factors considered for the sample size estimate are: at least 80% power, assuming 20% effect size, a confidence level of 95%, a correlation among repeated measures of 0.3, and an intra-class correlation within clusters of 0.05. Further, we assume equal numbers of clusters between CG and IG, and clusters within those conditions to be of equal size. Based on these assumptions, a baseline number of 15 participants per site was needed. This was, however, adjusted for several assumed losses. Based on knowledge of healthcare in this area and among target participants, the following participant loss estimates were made: healthcare transfers out of study sites at 5%, participant moving out of study area at 5%, deaths during the study at 7%, and study withdrawal/dropout at 5%. This results in a total of 22% dropouts, requiring an additional three participants (15 × 0.22) for a total of 18 participants per site. Additionally, we anticipate a 30% rate for declining to participate. Hence, we will need to approach an additional five ALHIV (18 × 0.3) for a total of 23 ALHIV currently enrolled as taking ART at study initiation to ensure that the requirement of 18 participants per site is met. Therefore, for two arms across six zones, we have a recruitment goal of 276 ALHIV (23 × 2 × 6) with a desired final sample size of 216 ALHIV (18 × 2 × 6) consented to participate. Sample size estimation was performed using G*Power (v. 3.1.9.1, Universität Düsseldorf, Germany) and Sampsize (v 0.6, P. Glaziou, ampsize.sourceforge.net) with appropriate adjustments for cluster randomization [44].

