For secondary objective 2, the study will assess whether the ACT intervention leads to improvements in the social, emotional, and psychological wellbeing of study participants; improvements in their self-efficacy; or changes in their health locus of control (HLC) from an external to an internal locus of control. Additionally, ACT aims to understanding the potential of psychologically based intervening variables to influence important study outcomes (i.e., increased retention rates and suppressed viral load). To examine important temporal changes in psychological factors, mean changes will be calculated for HLC, FSSQ, MHC-SF, and SRBBS scores from the transfer baseline to 12 and 24 months post transfer. Additionally, between-group comparisons will be made using repeated-measures analysis of variance (ANOVA). Owing to multiple tests among the same subjects, an approximate type 1 error of .05 will be maintained either directly through the use of a technique designed to accommodate repeated-measures designs (e.g., RM-ANOVA), or through the use of post-hoc adjustment of *p* values (e.g., Bonferroni’s method).

Simultaneously, ACT will examine direct and indirect contribution of psychosocial factors on viral-load suppression and retention of study participants in both study arms through multiple mediation model analyses as recommended by Preacher and Hayes [45]. Mediation analyses are particularly useful in randomized control trials as they attempt to capture the effects or processes that occur after randomization. As noted by Preacher and Hayes, the multiple mediation model is preferred over the traditional simple mediation model [45]. Additional mediator/moderator models will also be explored in order to investigate the potential direct and indirect impacts of other ACT intervention components; these will include the use of peer-led support groups during the pre- and post-transfer period, and the relative impact of case management support on retention rates and viral-load measures.

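### Two primary retention outcomes are tested separately with no order, level or success rule, and the psychosocial error-control sentence can be met by RM-ANOVA alone, which does not cover the four scales

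*Protocol article*

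**What the plan says.** **Primary outcomes.** The Outcome measures section of the protocol article defines retention at two times and concludes: "Hence, there are two primary outcome measures, with the long-term (24-month) retention measurement being a necessary" composite of those already retained in the short term. The 24-month definition asks for "at least four visits each separated by at least 6 months within 24 months post transfer". Under Statistical analysis, the hypothesis is directional (the intervention group's "percentages will exceed CG percentages from baseline to 12 months", and likewise to 24 months), and "An initial test of proportions will be conducted at each time period to compare these percentages using a one-way test". The section gives no order for the two tests, no significance level for either, and no rule on whether one or both must succeed. The nearest thing to a level is in Sample size estimation, which lists "at least 80% power, assuming 20% effect size, a confidence level of 95%, a correlation among repeated measures of 0.3", with no side and no allocation between the two outcomes.

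**Psychosocial outcomes.** The only sentence on multiplicity belongs to secondary objective 2. It gives multiple testing in the same participants as the reason, and says an approximate type 1 error of .05 is kept "either directly through the use of a technique designed to accommodate repeated-measures designs (e.g., RM-ANOVA") or by post-hoc adjustment of p values, with Bonferroni as the example. It does not say which tests form the family, and it does not choose between the two options. The scores concerned are HLC, FSSQ, MHC-SF and SRBBS, with changes from transfer to 12 and 24 months.

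**The concern.** With two primary outcomes and two tests, the error rate of the trial's main claim depends on what counts as success. The hypothesis under Study objectives and hypotheses is a single statement that retention will be significantly higher, so a win at either time could later be offered as confirming it. Nothing in the article rules that out.

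The psychosocial sentence has a different fault, because it states a method. RM-ANOVA deals with correlated visits within one score. It does nothing about testing four different scores. A team that picks the first option complies with the sentence as written and still leaves the four between-group tests unadjusted. The objective is framed so that one gain might be enough: it lists improved wellbeing, improved self-efficacy, or a shift in locus of control. At stake are a primary claim whose error rate is not fixed in advance, and a wellbeing claim whose error rate could be well above the stated .05.

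**Working it through.** **1. Are the two primaries nested?** Four visits at least 6 months apart within 24 months require the fourth by month 24, the third by month 18, the second by month 12 and the first by month 6. Someone retained at 24 months therefore has two visits at least 6 months apart within 12 months. The outcomes are nested, as the article says. Nesting makes the tests positively correlated but not identical: a significant 24-month test does not imply a significant 12-month test.

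**2. Correlation of the two tests.** Let p12 and p24 be the retention proportions. For nested binary outcomes the covariance is p24(1 − p12), so

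ρ = √[ p24(1 − p12) / (p12(1 − p24)) ].

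The article gives no retention rates, so these are assumptions: 70–85% at 12 months and 60–75% at 24.

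**3. Family-wise error if either success counts.** This is 2α − P(both tests reject), with the joint probability from a bivariate normal with correlation ρ. Each test is taken to hold its nominal level; any effect of clustering on the tests is a separate matter.

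| p12 / p24 (assumed) | ρ | α = 0.05 one-sided each | α = 0.025 one-sided each |
|---|---|---|---|
| 0.70 / 0.60 | 0.80 | 0.075 | 0.039 |
| 0.75 / 0.65 | 0.79 | 0.076 | 0.039 |
| 0.80 / 0.70 | 0.76 | 0.077 | 0.040 |
| 0.85 / 0.75 | 0.73 | 0.079 | 0.041 |
| 0.80 / 0.60 | 0.61 | 0.084 | 0.044 |

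Worked row: for 0.80 / 0.60, ρ = √[0.60 × 0.20 / (0.80 × 0.40)] = √0.375 = 0.61; P(both) = 0.016; 2 × 0.05 − 0.016 = 0.084. The most extreme pairing inside the assumed ranges, 0.85 / 0.60, gives ρ = 0.51 and 0.087. Independent tests would give 1 − 0.95² = 0.0975 at 0.05 each and 0.049 at 0.025 each.

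**4. Does the sample size reveal the level?** The stated base is 15 per site. The design effect is 1 + 14 × 0.05 = 1.70.
- Repeated-measures ANOVA, between-group effect f = 0.20, correlation 0.3, three measurements (f and the number of measurements are assumed): N = 108; 108 × 1.70 = 183.6; 183.6 / 12 = 15.3 per site, close to the stated 15.
- One-sided test of proportions with a 20-point difference: 16.2 per site (65% v 85%) and 13.9 (70% v 90%).
- Two-sided test of proportions: 17.6 per site (70% v 90%) and 13.9 (75% v 95%).

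Fifteen lies within both the one-sided and the two-sided ranges, and a calculation on means also reaches it. The sample size therefore does not settle the level or side of the primary tests.

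**5. Four scales, each with one RM-ANOVA between-group test at 0.05.** If they are independent, 1 − 0.95⁴ = 0.185. With an assumed common correlation between scales, simulation of four correlated two-sided tests gives:

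| Between-scale correlation | Chance of at least one false positive |
|---|---|
| 0 | 0.185 |
| 0.3 | 0.174 |
| 0.5 | 0.156 |
| 0.7 | 0.131 |

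With 0.0125 per scale the independent figure is 1 − 0.9875⁴ = 0.049.

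**The case against.** The best defence is that this is a protocol article. Test order, allocation of alpha and the success rule usually sit in the analysis plan, which is not shown. The article also calls retention at 12 and 24 months the primary outcome measure in the singular, states one retention hypothesis, and describes the 24-month outcome as building on the 12-month one. A both-required or hierarchical reading is as open as an either-wins reading. For the scales, the sentence follows text on change over time, so RM-ANOVA may be offered only for repeated visits, where it is appropriate. Bonferroni is named in the same sentence, and error control across secondary scales is not universally required.

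Much of this stands, and it limits the point in three ways.

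- A reader might infer that the chance of a false primary claim is above 5% as the plan is written. The article does not support that. It needs an either-wins rule and one-sided 0.05 for each test, and the article fixes neither.
- A reader might infer that the article says RM-ANOVA controls error across the four questionnaires. It does not: the family is never named.
- A reader might infer that a Bonferroni split of the primaries could never reach significance with six matched pairs. That would use the two-sided minimum, 2/64 = 0.031. For a one-sided test the minimum is 1/64 = 0.016, below 0.025, and the article does not say that permutation is at pair level.

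The defence does not answer everything. The article itself fixes two primaries with separate tests, so the missing rule concerns something it has already committed to. The either/or is a stated method, and its first option, used alone, leaves the stated .05 unmet across the scales.

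**Conclusion.** The point holds in conditional form.

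For the primaries, the article leaves the error rate of the main claim open. It is about 7.5–8.4% if either outcome suffices and each is tested at one-sided 0.05, under the assumed retention rates. It is about 3.9–4.4% at one-sided 0.025 each. It is at most the chosen level if both must succeed or the tests are ordered.

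For secondary objective 2, the family of tests is undefined, and one of the two permitted methods does not act across the scales. Relying on it alone gives about 13% (correlation 0.7) to 18.5% (independent scales) if a gain on any one scale supports the wellbeing claim. That any-scale rule is an assumption. It is a fair reading of how the objective is worded, but the article does not state it. If the adjustment option is taken across the four scales, the stated .05 is met.

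This should be corrected. It does not undermine the design.

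**What to change.** **Primaries.** State one significance level and its side, and reconcile them with the 95% confidence level in the sample size section. Then either test in a fixed sequence (for example 12-month retention first, and 24-month retention only if the first is significant) or require both to be significant. Neither rule needs an alpha split, whatever the dependence between the tests. In the sequence, if the 12-month null is true, any false claim must begin by rejecting it, which has probability at most α; if it is false, only the 24-month test can err, again at most α. The cost is that the later outcome cannot be claimed if the first fails, or that neither can be claimed alone if both are required. A Bonferroni split would also control the error, but with 90 per arm and design effect 1.70, one-sided power falls from 0.83 to 0.74 for an assumed 70% v 90%, and from 0.73 to 0.62 for 60% v 80%.

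**Psychosocial scales.** Replace the either/or with both parts: RM-ANOVA or a mixed model within each scale for the repeated visits, and a Holm adjustment across the four scales' between-group tests. Name those four tests as the family. The cost is slightly less power per scale, because the smallest p value must first meet 0.05/4 = 0.0125.

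The change is a few sentences of analysis wording. It should be made before outcome data are examined by arm, because a time point or adjustment chosen afterwards could not be defended.
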